#### Subgroup analysis

Socio-demographics▪ Age▪ Gender (male/female)▪ Body Mass Index (BMI)▪ American Society of Anaesthesiologists (ASA) class▪ Smoking (yes/no)Type-2 odontoid fracture subgroup▪ Grauer classification [15]Type of posterior C1–C2 fusion▪ Goel-Harms technique or Magerl-Atlas claw techniqueOsteoporosis (dual energy x-ray absorptiometry (DXA) score)

### Participant timeline

The Consolidated Standards of Reporting Trials (CONSORT) inclusion flow diagram is presented in Fig. 1 [26]. The USOFT participant timeline is described in Fig. 2.

**Fig. 1 Fig1:**
[figure not shown]
Consolidated Standards of Reporting Trials (CONSORT) inclusion flow diagram

**Fig. 2 Fig2:**
[figure not shown]
Participant timeline. *CT* computed tomography, *CCI* charlson comorbidity index, *EQ-5D* euroQol, *NDI* neck disability index, katz *ADL* activities in daily life according to katz, *DXA* double x-ray absorptiometry

### Recruitment

The history and physical examinations of all patients scheduled for surgery are screened preoperatively for predictors of difficult airways. Patient recruitment is conducted by a physician, while patient-reported follow-up is controlled by a qualified study nurse.

### Assignment of intervention

#### Allocation

When a patient with an eligible type-2 odontoid fracture seeks care at the hospital, the surgeon in charge of emergency care will contact the study group who inform the patient about the study and obtains their informed consent (Additional file 2). If the patient is unable to give informed consent, a close relative will be asked to give permission. Allocation is randomised using a sequentially numbered, opaque, sealed envelope (SNOSE) technique [27]. For obvious reasons, this study is not blinded.

If the patient/relative chooses not to participate in the USOFT, the patient is treated with a rigid collar, i.e. the present treatment at the department. Socio-demographic and clinical data will be collected. After acute treatment and mobilisation, the patient will be discharged to a suitable level of care in a normal way.

#### Sequence generation

Simple randomisation will be used to generate the allocation sequence. Randomisation is concealed using a SNOSE technique. Once a patient has given written consent, the next envelope according to the numbered sequence is opened and the patient is treated according to the allocated treatment.

#### Blinding

Blinding is not possible.

### Study instruments

#### Neck Disability Index

The NDI quantifies neck-related disability on a score from 0 (no disability) to 50 (maximum disability) [24]. The results are then transformed into percentages (50 point = 100% disability). As many of the patients aged ≥ 75 years no longer drive a car, question 8, which concerns driving a car, may be excluded, resulting in a maximum score of 45. The minimal clinically important difference (MCID) of the NDI is 3.5 points, with a standard deviation (SD) of 3.5 points [28]. The modified Swedish version of the NDI has been tested, showing good validity, sensitivity, test-retest reliability and specificity [25].

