### Study outcome measures

#### Primary outcome measure

The primary outcome variable is the difference in the Neck Disability Index (NDI) at baseline and 1 year after injury [24, 25]. Both comparing differences within the groups (baseline vs. NDI at 1 year), but also differences between the groups. The same evaluation will be made at 6 weeks and 3 months.

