### Statistics

For statistical analysis, R version 3.4.1 (R Foundation for Statistical Computing, Vienna, Austria) will be used. The results will be presented according to the CONSORT Statement for non-pharmacological interventions [26]. The analysis will be performed by intention-to-treat (ITT), and sensitivity analyses will include a per-protocol analysis.

Missing values will be imputed using multiple imputation by use of chained equations as implemented in the R package “mice” with 20 iterations [40]. Details of the statistical analysis are listed in Table 1.

**Table 1 Tab1:** Variables, measures and methods of analysis

Variable/Outcomes	Hypothesis	Outcome measures	Methods of analysis
*Baseline data:*	There is no difference between the two groups	Gender, age, Katz ADL, CCI, nursing home/hospitalisation, smoking status	Absolute numbers, percentages for categorical variables and the minimum, maximum, mean, SD and quartiles for quantitative variables
*Primary:*			
Function	There is a clinically important difference between the two groups, with improvement comparing baseline data with data from 6 weeks, 12 weeks, and 1 year. Surgical treatment is hypothesised to be superior	NDI (0–100%) [continuous]	Student *t* test, chi-square, Mann-Whitney, Fisher’s exact test. Time-dependent differences between AUC
*Secondary:*			
Health-related quality of life	There is a clinically important difference between the two groups	EQ-5D [continuous]	Student *t* test, chi-square, Mann-Whitney, Fisher’s exact test Time-dependent differences between AUC
Pain	There is a clinically important difference between the two groups	VAS (0–100) [continuous]	Students *t* test, chi-square, Mann-Whitney, Fisher exact test Time-dependent differences between AUC
Non-union	The non-union rate is lower in the surgical group	Bone bridge in CT [binary], mobility on extension-flexion radiographs [binary],	Chi-square test
Mortality	The survival is greater in the surgical group	all-cause mortality [binary], time to death [continuous, censored]	Kaplan-Meier analysis, Cox regression models, additional subdistribution hazards approach
Osteoporosis	There is no difference between the two groups	The bone density is > 2.5 standard deviations below normal DXA T-score [binary]	Chi-square
*Subgroup analysis:*			
septuagenarians vs. octogenarians vs. nonagenarians	Treatment effect is diminished in nonagenarians		
Goel-Harms technique vs. Magerl technique	There is no difference between the two groups		

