### Sample size

Up to 50 participants will be included in the study, based on the following calculation of sample size:

The MCID of the NDI is 3.5 points (7%) and the SD is 3.5 points [28]. Thus, 16 participants are needed in each group to reach 80% power with a two-sided significance level of *p* < 0.05 in a (clinically important) superiority study design. Adjusting for 1-year mortality among those aged ≥ 70 years with a non-surgical axis fracture treatment of 29% (Robinson AL et al. Spine J. 2018; in press), eight additional participants must be recruited in each group. A minimum of 24 subjects must be included in each group.

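### The driving item of the NDI is optional, but the item set and denominator are not fixed, while the percentage conversion and the MCID stay on the 50-point base

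*Protocol article*

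**What the plan says.** The section Neck Disability Index, under Study instruments, defines the instrument: "The NDI quantifies neck-related disability on a score from 0 (no disability) to 50 (maximum disability". One conversion follows: "The results are then transformed into percentages (50 point = 100% disability". The section then gives a reason for leaving out an item, "As many of the patients aged ≥ 75 years no longer drive a car", and the consequence: "question 8, which concerns driving a car, may be excluded, resulting in a maximum score of 45". It gives no second conversion and no rule on who decides, for which patients, or at which visits.

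Three other places use the score:

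- Primary outcome measure: "The primary outcome variable is the difference in the Neck Disability Index (NDI) at baseline and 1 year after injury". Differences are to be compared within and between groups, with the same evaluation at 6 weeks and 3 months.
- Statistics, Table 1: the outcome is listed as "NDI (0–100%) [continuous".
- Sample size: "The MCID of the NDI is 3.5 points (7%) and the SD is 3.5 points".

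The section Data monitoring bases the interim stopping test on NDI improvement as well.

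**The concern.** The statements do not fit together without a rule that the article does not give. A form with a maximum of 45 cannot fill a 0–100% range if 50 points is 100%. If 45 points is 100% instead, 3.5 points is no longer 7%. The stated reason is that many patients no longer drive, which does not mean all of them, so a mixture of nine-item and ten-item forms is the natural expectation.

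Two things are at stake. Patients may be scored on unequal scales. And because the primary outcome is a change from baseline, a different item set at the two ends of one patient's follow-up enters the endpoint directly. The trial is open-label, so whoever leaves out an optional item knows the treatment arm. Simple randomisation of about 50 people also gives no assurance that non-drivers are evenly split.

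**Working it through.** **Inputs (all from the protocol article).** Ten-item maximum 50; nine-item maximum 45; 50 points = 100% (Neck Disability Index). MCID 3.5 points = 7%, SD 3.5 points, 16 per group at 80% power and two-sided 0.05 (Sample size).

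**The plan's own figures.**
- Weight of item 8: 50 − 45 = 5 points.
- MCID as a percentage: 3.5/50 = 7.0%. On 45 points it is 3.5/45 = 7.8%; conversely, 7% of 45 is 3.15 points.
- Sample size: n = 2 × (1.96 + 0.84)² × (3.5/3.5)² = 15.7, so 16 per group. This reproduces and is not affected by the point made here.

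**Case 1: item 8 absent at every visit, denominator 50 kept.** The percentage is 45/50 = 0.9 times the 45-based value.

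| Disability on 45-point base | Nine-item sum | Sum/50 | Shortfall |
|---|---|---|---|
| 20% | 9 | 18% | 2 |
| 40% | 18 | 36% | 4 |
| 60% | 27 | 54% | 6 |
| 80% | 36 | 72% | 8 |
| 100% | 45 | 90% | 10 |

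These are shortfalls in score level, in percentage points. The primary outcome is a change, and for a patient who never answers item 8 the change also shrinks by 10%: a 7% change becomes 0.9 × 7 = 6.3%, a loss of 0.7.

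**Case 2: item 8 answered at baseline, left out at 1 year, denominator 50, other nine items unchanged.** The apparent improvement equals the item-8 score q, or 2q in percent: q = 1, 2, 3, 4, 5 gives 2, 4, 6, 8, 10%. Only q = 4 or 5 exceeds 7% (3.5 points). The reverse switch gives a false worsening of the same size.

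**Case 3: the same switch, nine-item form rescaled to 45.** With ten-item total T, the apparent improvement in percent is 100 × [T/50 − (T − q)/45] = (10q − T)/4.5.
- It is zero only when q = T/10, that is, when item 8 equals the patient's mean item score.
- It never exceeds the 2q of Case 2, because q cannot exceed T.
- It exceeds 7% for q = 5 with T up to 18 ((50 − 18)/4.5 = 7.1) and for q = 4 with T up to 8 ((40 − 8)/4.5 = 7.1), and for no lower q.
- It becomes a false worsening when q is below T/10.

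Rescaling therefore lessens the false improvement but does not remove the artefact. A constant item set does.

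**Case 4: item 8 dropped for everyone at every visit.** There is no switching, but the 50-point conversion no longer applies to any form, and 3.5 points is 7.8%, not 7%.

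**Between-arm difference.** The article gives no switching rate, so the following range is assumed. With an excess f of Case 2 switchers in one arm and mean item-8 score m, the arm difference shifts by f × m points. For f = 10% and m = 2 this is 0.2 points (0.2/3.5 = 6% of the MCID). For f = 40% and m = 4 it is 1.6 points (1.6/3.5 = 46%).

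**The case against.** The strongest defence is that the article never says nine-item forms are divided by 50. Stating a new maximum of 45 may be meant as a new base, and a 0–100% range can be filled by nine items only on that base. Likewise, the permission to exclude the item could apply to the whole trial, with no mixing at all. The stated ground is that people of this age no longer drive, not that the neck injury stopped them. A journal article also condenses the full protocol, which may hold the scoring rule, and the scoring of the cited Swedish version of the instrument cannot be seen.

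Much of this stands. A reader might infer that the plan under-scores non-drivers, or that patients who stop driving will appear to improve by more than the MCID. The documents support neither as a statement of fact. The first depends on keeping 50 as the denominator, which is left open. The second needs item 8 to be answered and later omitted, with a score of 4 or 5, and is an artefact in a single patient rather than a shift in the trial's estimate. Nor should the 4-point and 6-point level shortfalls in Case 1 be set against the MCID as if they were errors in change.

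The defence does not remove the point. The article does more than stay silent on scoring: it states a conversion, an exclusion, a new maximum, an analysis range and an MCID equivalence, and each reading leaves one of them wrong. Dividing by 50 conflicts with the 0–100% range, and dividing by 45 breaks the 7% equivalence and still leaves the switching artefact. Dropping the item for all patients makes the stated conversion inapplicable.

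**Conclusion.** The point holds as a badly fixed scoring rule for the primary endpoint, one that should be corrected before analysis. If 50 is kept as the denominator, nine-item forms are capped at 90%, and scores and changes are 10% too small relative to a 45-point base. If a patient's item set changes between baseline and 1 year, the raw change shifts by the item-8 score, at most 5 points against an MCID of 3.5.

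Whether the between-arm difference is biased, and by how much, depends on unequal numbers of non-drivers or switchers by arm. The article gives no figure for either, so the 0.2 to 1.6 points above is an illustration under assumed rates, not an estimate.

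**What to change.** State in the protocol or analysis plan:

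1. One item set per patient, used at every visit: either item 8 is in or out according to whether the patient drove before the injury, or the nine common items are used for everyone.
2. Percentage score = sum / (5 × items scored) × 100.
3. This percentage is the score for the primary analysis and the interim stopping test, with the MCID stated on the same scale.
4. A sensitivity analysis on the nine items common to all patients, if item 8 is kept for drivers.

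The cost is re-derivation of scores from the item-level forms, which must have been kept, and one question on driving before the injury. Using nine items for all avoids that question but gives up one item of the instrument. No additional patients are needed as long as the MCID and SD are moved to the new scale together, since the calculation depends only on their ratio (3.5/3.5 = 1).

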#### EuroQol health-related quality of life questionnaire (EQ-5D)

EQ-5D is a standardised self-rating instrument developed by the EuroQol group as a measure of HRQoL and translated into Swedish [29]. The EQ-5D consists of a descriptive system and the EQ Visual Analogue Scale (VAS). In the questionnaire, the study participant classifies their health in five dimensions (mobility, hygiene, main activities, pains/inconvenience, worry/mood) in one of three degrees (no problems = 1, moderate problems = 2, difficult problems = 3). The five questions in the health questionnaire make it possible to determine 243 different health conditions. The value may be negative, due to the conversion system, and varies between 1 and − 0.594. To enable health economic analyses (i.e. quality-adjusted life-years (QALY) calculations), each of the 243 health conditions has a quality of life tariff linked to it. In Sweden, we use the English tariff [30, 31].

EQ VAS (self-assessed health): the individual estimates a value for their current state of health on a scale graded from 0 to 100.

#### Katz ADL Index

The Katz ADL Index comprises six basic functions: bathing, dressing, toileting, transfer, continence and feeding. It provides an objective method of classifying and describing an individual’s health needs and outcomes. For each activity (six in total), there is a question. Each question has two possible answers: independent or dependent [32]. The Katz ADL Index is an ordinal scale ranging from A to G, where A means that the patient is totally independent of any assisting help. F is considered to be an indicator of a dependent patient. There is no ‘cut-off’ limit. The score will be transformed into a nominal scale (1–7) where A = 1, B = 2, etc.

#### Computer tomography

CT is the most reliable radiographic tool to classify and evaluate healing in relation to type-2 odontoid fractures [33]. Bony union is assessed by a radiologist, independently from the study. Healing is defined as ‘not visible fracture line’ or ‘bone bridging in fusion’.

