#### Non-surgical treatment

The patient will be provided with a well-fitted and rigid collar, such as the Philadelphia collar (Ossur, Sollentuna, Sweden) or the Aspen collar (Aspen Medical Collars, Irvine, CA, USA). The collar will be worn 24 h a day for 12 weeks. The collar may be removed for short periods of time for personal hygiene when the patient is supine in bed.

CT scans will be repeated after 1 week, 6 weeks and 3 months. In case of increasing fracture displacement, or symptomatic non-union, the fracture will be treated surgically with a posterior C1–C2 fusion. The crossover will be documented, but all data will be analysed according to the intention-to-treat (ITT) principle.

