#### Surgical treatment

The patient will be surgically treated with an instrumented posterior C1–C2 fusion, including an autologous iliac crest bone graft. The primary fixation technique involves transarticular C1–C2 screws, according to Magerl, and the C1 claw device [20]. In case of anatomical aberrations or a concomitant C1 arch fracture, other techniques may be used: e.g., C1 screws, according to Goel-Harms [21, 22], or translaminar C2 screws, according to Wright [23].

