### Non-union

A chi-squared test will be used to compare the non-union rate between the two groups.

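### CT healing can be met through bridging in the fusion, a route closed to collar patients who have not crossed over, so the non-union comparison does not count the same event in both arms

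*Protocol article*

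**What the plan says.** The section on computed tomography under Study instruments gives the definition: "Healing is defined as ‘not visible fracture line’ or ‘bone bridging in fusion". The two criteria are joined by 'or', and neither is tied to an arm. The same section adds: "Bony union is assessed by a radiologist, independently from the study".

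Under Surgical treatment: "The patient will be surgically treated with an instrumented posterior C1–C2 fusion, including an autologous iliac crest bone graft". Under Non-surgical treatment, a collar patient can also receive a fusion: "In case of increasing fracture displacement, or symptomatic non-union, the fracture will be treated surgically with a posterior C1–C2 fusion". Such patients are analysed in the collar arm by intention to treat.

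Table 1 (Statistics) states the hypothesis "The non-union rate is lower in the surgical group" and lists the measure as "Bone bridge in CT [binary], mobility on extension-flexion radiographs [binary", which mentions neither the fracture line nor the fusion. The Non-union section gives the test: "A chi-squared test will be used to compare the non-union rate between the two groups". Bony union at 1 year is among the secondary objectives. No expected union or bridging rate by arm is stated.

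**The concern.** Bridging in the fusion can occur only in a patient who has been fused. An operated patient with a persistent odontoid fracture line but a bridged C1–C2 graft is classed as healed. A collar patient with the same fracture line and no operation is classed as a non-union. The arms can then differ in the outcome without differing in fracture healing.

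A second distortion runs the other way. A collar patient fused for symptomatic non-union stays in the collar arm and becomes healed once the graft bridges, although failure to unite was the reason for the operation.

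At stake is the interpretation of a named secondary objective. The difference would be read as an effect of surgery on fracture healing, in a trial whose results are meant to inform guidelines, when an unknown part of it comes from the definition.

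**Working it through.** **Reading the definition.** There are two ways to read the 'or'.
- Inclusive: operated patients can be healed by either criterion, and collar patients who have not crossed over by one only.
- Arm-specific (fracture line for collar, bridging for surgery): the arms are compared on two different events.

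The criteria are unequal under both. Table 1 gives a third wording, a bone bridge on CT, which could mean a bridge across the fracture or within the fusion.

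**Number of CTs.** The protocol gives no sample size for non-union, so the figure must come from the NDI calculation. That calculation reproduces: with a difference of 3.5, an SD of 3.5, 80% power and two-sided 0.05, n = 2 × (1.96 + 0.84)² × (3.5/3.5)² = 15.7, hence 16 per group as stated. Allowing for 29% mortality, 16/0.71 = 22.5, hence 23, against the stated 24. Survivors with a 1-year CT: 24 × 0.71 ≈ 17 per arm.

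**Artificial gap.** All rates here are assumptions. Let u be the probability of odontoid union, equal in both arms, and g the probability of bridging among fused patients whose odontoid has not united.
- Collar, no crossover: healed = u
- Surgery: healed = u + (1−u)g
- Gap with no true difference in fracture union: (1−u)g

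**Crossover.** Let a share c of un-united collar patients be fused, bridge with the same g by 1 year and stay in the collar arm. Collar healed becomes u + (1−u)cg, and the gap becomes (1−u)g(1−c).

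The probability of a significant uncorrected chi-squared result in favour of surgery was enumerated exactly at 17 per arm:

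| u | g | c | Collar healed | Surgery healed | Gap (points) | Significant for surgery |
|---|---|---|---|---|---|---|
| 0.8 | 0.25 | 0 | 80% | 85% | 5 | 5% |
| 0.7 | 0.9 | 0 | 70% | 97% | 27 | 61% |
| 0.5 | 0.8 | 0 | 50% | 90% | 40 | 75% |
| 0.5 | 0.9 | 0 | 50% | 95% | 45 | 89% |
| 0.7 | 0.9 | 0.3 | 78.1% | 97% | 19 | 36% |
| 0.5 | 0.8 | 0.3 | 62% | 90% | 28 | 48% |
| 0.5 | 0.9 | 0.3 | 63.5% | 95% | 32 | 67% |

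For example, in the fourth row (1−0.5) × 0.9 = 0.45, and in the last row 0.45 × (1−0.3) = 0.315.

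With one fracture-site criterion in both arms and equal union, the gap is 0 and the chance of a significant result in favour of surgery is about 2–3%.

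**The case against.** The strongest defence is that the operation aims at a solid C1–C2 fusion, so bridging in the fusion is its natural bony endpoint. For a pragmatic question, whether the allocated strategy ends in solid bone by either route, a composite of fracture healed or fusion solid is legitimate. That stands, but the protocol calls the outcome healing and non-union and does not present it as such a composite. On that view the components still need to be reported separately.

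It can also be said that the reader is independent and that stability is judged by one threshold in both arms (more than 3.5 mm listhesis and/or more than 11° angulation). An independent reader still applies an unequal rule. Stability is a useful common measure, but a fusion itself confers it, so it does not replace fracture union.

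Crossover to fusion under intention to treat does narrow the gap, so it would be too absolute to say that collar patients lack the second route altogether. It is not a safeguard, however. It partly offsets one unknown bias with another and makes the collar-arm rate harder to read.

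A reader might infer that the directional hypothesis in Table 1 is itself a defect. It is not: the chi-squared test of two proportions is two-sided, and a stated expectation does no harm.

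**Conclusion.** The criterion is unequal between the arms under either reading of the 'or', and the between-arm non-union rate cannot be read as a comparison of fracture healing. Table 1 does not match the definition, so the endpoint is worded in two ways.

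A reader might infer that a surgical advantage in non-union would be largely built in. The document does not support that. It gives no odontoid union or fusion bridging rate by arm and no crossover rate. The only healing figure, 88%, comes from an uncontrolled surgical cohort. Over the assumptions shown, the artificial gap runs from 5 points (significant in about 5% of trials) to 45 points (89%), and 30% crossover reduces the latter to about 32 points (67%). These figures assume equal true union in both arms, 17 CTs per arm and, for the crossover rows, the same bridging rate in crossovers as in patients allocated to surgery.

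The consequence is confined to a secondary outcome. The primary NDI comparison and its sample size do not depend on it. The change should be made, but the primary conclusion does not hang on it.

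**What to change.** - Make the between-arm CT outcome odontoid fracture union, judged by one fracture-site criterion in both arms.
- Report bridging of the C1–C2 fusion separately and descriptively, in all operated patients including crossovers.
- State how many collar-arm patients were fused and give their fracture-site status on CT. Whether to recode them as non-unions is a choice of estimand on which the plan should be explicit; the repair does not depend on it.
- Reconcile the definition in the computed tomography section with the measure in Table 1.

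The cost is a change of wording and one extra item on a CT that the same radiologist already reads, with no extra scan. The surgical healing figure may look less favourable once fusion bridging no longer counts as fracture union.
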